### Data monitoring & interim analysis

A data and safety monitoring board (DSMB) comprised of professionals with expertise in neonatal and child health will oversee the safety of the trial. Each DSMB member will be independently responsible for making recommendations for stopping the study based on specific safety endpoints.

Biannual interim analyses will examine the primary and secondary outcomes as well as iNCK compliance measures. The DSMB will convene annually, and at least two weeks prior to each meeting, the panel members will be given a written report outlining the current status of the study, masked outcome data, and information pertaining to any adverse events that may have occurred. If the mortality difference becomes higher than 40% in either direction (i.e., 40% greater mortality in the intervention or control clusters), the DSMB will be unmasked, and a decision will be made on whether the trial should continue.

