### Sample size

With the initially planned 39 clusters per trial arm, an average of 306 live births per cluster (23,868 pregnant women and live-born newborn pairs) is required to achieve 80% statistical power to detect a relative reduction of 25% in all-cause neonatal mortality. Sample size calculations were based on an assumed NMR of 35 newborn deaths per 1,000 live births in control clusters and an estimated intracluster correlation coefficient of 0.002 [16]. Furthermore, to allow for up to 5% attrition due to stillbirths and 10% attrition due to losses to follow-up, we aim to enroll a total of 27,448 pregnant women over a period of approximately 26 months.

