### Statistical analysis plan

Hypothesis testing for this study will be based on a superiority framework and will be conducted at the α = 0.05 significance level. Primary analyses will be conducted using a complete-case, intention-to-treat approach, where participants will be analyzed in the trial arm their cluster was randomized to, irrespective of contamination or adherence to instructions on how to use the iNCK. The unit of analysis will be the individual neonate (neonatal mortality, omphalitis, fever, hypothermia, and healthcare utilization for newborn morbidities) or the individual woman (PPH and healthcare utilization for PPH). Risk ratios for the primary (neonatal mortality) and secondary (omphalitis and PPH) outcomes will be estimated using multivariable modified Poisson regression [29], with generalized estimating equations to account for the clustered design and robust variance estimators to account for multiple births and/or multiple pregnancies during the study period. Analyses of neonatal mortality (the primary outcome) will adjust for newborn sex, antenatal care, and gestational age at birth to improve power and efficiency; calendar time to account for underlying temporal trends (defined as month of birth, setting month of study launch as month 0); and the covariates used in the randomization procedure: GB study district, log cluster-specific baseline NMRs, and the cluster-specific baseline proportion of children delivered at a health facility. Analyses of omphalitis (secondary outcome) will adjust for newborn sex, antenatal care, and GB study district. Analyses of PPH (secondary outcome) will exclude women who delivered via C-section, and will adjust for parity, maternal age, history of prior C-section, history of prior PPH, GB study district, and the cluster-specific baseline proportion of women who reported experiencing PPH. The frequency of hypothermia, cold stress, and fever detected by ThermoSpot™ within the first 14 days of life will be described amongst participants in intervention clusters only, overall and by calendar month to assess seasonality. Finally, the frequency and location of health facility utilization for omphalitis, PPH, hypothermia, and fever will be described using counts and proportions amongst individuals experiencing each respective morbidity and will be stratified by trial arm. The proportion accessing healthcare services by trial arm will be compared using clustered t-tests and modified Poisson regression.

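### A fixed 40% mortality ratio is the only stated condition for unmasking the DSMB, and it becomes less sensitive to moderate excess mortality as data accumulate

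*Protocol article*

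**What the plan says.** The section on data monitoring and interim analysis (Protocol article) states: "Biannual interim analyses will examine the primary and secondary outcomes as well as iNCK compliance measures". It then says "The DSMB will convene annually" and that members receive masked outcome data beforehand. The condition for lifting the mask is "If the mortality difference becomes higher than 40% in either direction (i.e., 40% greater mortality in the intervention or control clusters"). When it is met, "the DSMB will be unmasked, and a decision will be made on whether the trial should continue". No number of deaths, standard error, p-value or boundary is attached to the 40%. It is the same in both directions and at all times. The text does not say whether it is applied at the biannual analyses, at the annual meetings, or at both.

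The statistical analysis section says testing "will be conducted at the α = 0.05 significance level" within a superiority framework. The sample size section plans for a 25% relative reduction.

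**The concern.** A fixed ratio carries very different evidence at different times. Early on, when deaths are few, chance alone can produce a 40% difference. Late on, a 40% difference is far beyond any usual level of significance, and a smaller excess that is already statistically clear does not meet the condition. As the estimate settles around its true value, any true excess below 40% becomes less likely to cross the trigger at a given look. A harm safeguard should behave the other way round.

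Mortality is the primary outcome, and this rule decides when the board sees it by arm. At stake is whether a real, moderate excess of newborn deaths in the intervention clusters would prompt unmasking. A second issue is that the benefit trigger of 1/1.40 = 0.714 sits beside the planned risk ratio of 0.75, so a trial that works as designed will often be unmasked.

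**Working it through.** **Inputs (sample size section).** "With the initially planned 39 clusters per trial arm, an average of 306 live births per cluster"; 23,868 births in total; control mortality 35 per 1,000; intracluster correlation (ICC) 0.002; planned risk ratio (RR) 0.75; enrolment over about 26 months. **Assumed:** uniform accrual, equal clusters, 39 per arm, a crude RR, two-sided p-values, looks at months 6, 12, 18 and 24 (biannual) or 12 and 24 (annual), and an outcome lag of 0 to 3 months. Some lag is realistic, because women enrol in the third trimester and outcomes are collected from day 29.

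**The plan's own figure.** The article gives no operating characteristics for the trigger, so there is none to reproduce. The 306 births per cluster do not follow from the stated inputs alone. With 6,086 per arm before clustering, m = 6,086 × 0.998 / (39 − 6,086 × 0.002) ≈ 226. An ICC of about 0.0032 would give roughly 306. That is a separate matter. I use 306 as stated and check 0.0032 below.

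**Formulas.** N = 23,868 × (month − lag)/26; births per cluster m = N/78; design effect D = 1 + (m − 1) × 0.002. With control risk p₀ = 0.035 and N/2 births per arm, Var(log RR) = D × [(1 − p₀)/(p₀N/2) + (1 − p₀·RR)/(p₀·RR·N/2)]. The trigger is |log RR| > ln 1.4 = 0.3365.

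**Worked example, month 24, no lag.** N = 22,032; m = 282.5; D = 1.563; about 386 deaths per arm if RR = 1. Var = 1.563 × 2 × 0.965/385.56 = 0.00782, so SE = 0.0885 and z at RR 1.40 = 0.3365/0.0885 = 3.80. With true RR 1.25 (about 482 against 386 deaths), SE = 0.0837. The chance of crossing is 1 − Φ((0.3365 − 0.2231)/0.0837) = 1 − Φ(1.35) ≈ 9%, although the expected z is 0.2231/0.0837 = 2.66.

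**All looks, no lag:**

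| Month | Deaths per arm if RR = 1 | SE if RR = 1 | z (p) at RR 1.40 | Observed RR reaching p = 0.05 | Crosses if true RR 1.25 | Crosses for benefit if true RR 0.75 |
|---|---|---|---|---|---|---|
| 6 | 96 | 0.151 | 2.23 (0.026) | 1.34 | 21% | 38% |
| 12 | 193 | 0.113 | 2.97 (0.003) | 1.25 | 15% | 35% |
| 18 | 289 | 0.097 | 3.45 (0.0006) | 1.21 | 11% | 32% |
| 24 | 386 | 0.0885 | 3.80 (0.00014) | 1.19 | 9% | 31% |

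With a 3-month lag, p at RR 1.40 is 0.10, 0.008, 0.001 and 0.0003 at the four looks. The chance of crossing with true RR 1.25 is 28% at month 6 and 10% at month 24.

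An observed RR of 1.39 at month 24 (no lag) gives z = ln 1.39/0.0885 = 3.72, p ≈ 0.0002, and does not meet the stated condition.

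**Cumulative probabilities** (simulated correlated looks; no lag to 3-month lag):

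| | Annual | Biannual |
|---|---|---|
| True RR 1.25, current trigger (harm side) | 17–21% | 29–37% |
| True RR 1.25, one-sided z > 2 | 77–74% | 80–77% |
| RR = 1, one-sided z > 2 | about 4% | 5–6% |
| True RR 0.75, current trigger (benefit side) | 42–45% | 54–60% |

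**Type I error.** Suppose every trigger were counted as a rejection and the final test stayed at 0.05. Without lag the total would be about 5.1% (annual) or 6.9% (biannual). With lag it is higher if the trigger is applied at month 6, reaching about 15% at the top of the range.

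**Sensitivity.** With ICC 0.0032 and no lag, p at RR 1.40 runs from 0.03 (month 6) to 0.0006 (month 24). A 25% excess is flagged cumulatively 19% (annual) or 30% (biannual) of the time. The pattern is unchanged.

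**The case against.** The strongest reply is that this is a prompt to unmask and decide, not a stopping or efficacy boundary. That stands. A reader might infer that the rule inflates the false-positive rate to 7–15%. The document does not support this, because that result needs every trigger to stop the trial and be claimed as a finding, and its upper end also needs outcome lag and a look at month 6.

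Three other tempting readings also go too far:

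- **Too loose at the first look.** This holds at month 6 only. At a first annual meeting p is about 0.003 (0.008 with a 3-month lag); without lag that is close to an O'Brien-Fleming-type level. The text does not say that the trigger is applied at month 6.
- **A coin flip under the planned effect.** This is true cumulatively, not at a single look (31–38% without lag). Unmasking an independent board when a large benefit appears is not in itself a fault.
- **No alpha control.** The article states none, but spending functions and boundaries commonly sit in an analysis plan or DSMB charter, which are not shown.

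Nor do biannual analyses and annual meetings contradict each other. The analyses also cover compliance, and the text does not require a meeting for each one.

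Finally, the trigger is not the only safeguard. Each DSMB member may recommend stopping on safety endpoints, and study-related adverse events are reported to the board. The masked data might also be shown by coded arm, though the article does not say so. These routes soften the concern but do not remove it. Adverse-event reporting is passive and compares nothing between arms, and the 40% ratio is the only unmasking condition stated.

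**Conclusion.** The concern holds for the rule as written, chiefly on the harm side. One ratio means p of about 0.03 at month 6 (0.10 with a 3-month lag) and 0.0001–0.0003 at month 24. A true 25% excess in newborn deaths would be flagged in roughly a fifth of trials with annual looks, or about three in ten to under four in ten with biannual looks. A one-sided z > 2 condition would flag about three quarters or more. Late in the trial, a highly significant excess just under 40% leaves the stated condition unmet.

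On the benefit side, closeness to the planned effect makes unmasking common, at 42–60% cumulatively depending on schedule and lag. This threatens type I error only if the trial is then stopped and benefit claimed.

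These figures rest on uniform accrual, equal clusters, a crude RR and the plan's own mortality and ICC. They also read 40% greater mortality in controls as RR below 0.714, which the article's own clarification supports. This should be fixed, but the documents do not show that it invalidates the trial.

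**What to change.** - Replace the fixed ratio with boundaries on the cluster-adjusted test statistic, different for harm and benefit. An example is one-sided z > 2 to unmask for harm, with a Haybittle-Peto or O'Brien-Fleming-type boundary for benefit.
- Keep the consequence as it is: unmasking and DSMB review, not an automatic stop.
- State whether the condition is applied at the biannual analyses, at the annual DSMB meetings, or at both.
- State the final significance level if alpha is spent for benefit.
- If a DSMB charter or analysis plan already sets boundaries, reconcile the published text with it.

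The cost is protocol and charter wording, with no extra data or participants. With z > 2, the harm condition would unmask falsely in about 4% (annual) to 6% (biannual) of trials with no true effect. The final critical value would rise very slightly above 1.96. With Haybittle-Peto at |z| > 3 and the final test left at 0.05, simulated overall alpha is only 0.051 (two looks) to 0.053 (four looks).

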### Adverse event reporting

The study will employ a passive adverse event reporting system. Should any potential adverse event be reported to the study team, a data collector or field supervisor will complete an Adverse Event Report Form and document the participant-reported details surrounding the event. This form will be electronically sent by the field supervisor to a study physician at Aga Khan Health Services, Pakistan (AKHS,P) for evaluation. If deemed to be study-related, the study physician will inform the principal investigator. Adverse events will be reported to the required regulatory bodies within 15 calendar days from the day the principal investigator becomes aware. The principal investigator will notify the DSMB about study related adverse events and, if deemed necessary, the DSMB will make recommendations to the principal investigator about stopping the trial.

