### Study outcome measures

The primary outcome measure is all-cause neonatal mortality, defined as the death of a live-born child from any cause within the first 28 days of life. Study outcomes (Table 2) will be measured on all enrolled participants.

**Table 2 Tab2:** Primary and secondary outcomes

Primary Outcome	**•**All-cause neonatal mortality among live born neonates in first 28 days of life
Secondary Outcomes	**•**Cumulative incidence of omphalitis
	**•**Cumulative incidence of post-partum hemorrhage (PPH)
	**•**Post-delivery health facility utilization by pregnant women, and/or neonates and mothers in the first month postpartum
	**•**Cumulative incidence of hypothermia within the first 28 days of life, as identified through use of the ThermoSpot™, and explore the seasonal variability (by month) in the cumulative incidence of hypothermia **•**Cumulative incidence of fever within the first 28 days of life, as identified through use of the ThermoSpot™
	**•**Compliance with instructions on how to use the iNCK
	**•**Cause-specific neonatal mortality as determined by verbal autopsy

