For the intervention phase of the trial, data collectors will complete one in-person at-home visit, a mid-point assessment call, and try for a second in-person at home visit. The first in-person visit will occur during the third trimester of pregnancy, at which time data collectors will screen potential participants for eligibility. If eligibility criteria are met, participants who provide informed consent to participate in the trial will receive a pictorial diary from the LHW to enable self-reporting regarding compliance for individual iNCK components (intervention clusters only). Data collectors will then administer a questionnaire in the form of a structured interview to collect sociodemographic and household data. On the 8^th^ day of a newborn's life, field supervisors will attempt to complete phone interviews with participant households to collect information surrounding the baby's delivery and study outcomes of interest that may have occurred during the first week of the newborn’s life. While efforts will be made to complete these calls on the 8th day of life, a one-week window will be permitted for completing this phone call (between the 8th day through the 14th day of the newborn’s life). If the study team is unable to contact the participant for this data collection touchpoint, data collectors will obtain this information during the in-person at-home visit on the 29th day of the baby’s life. Data collectors will visit participant households on day 29 of the newborn's life to collect information that will enable the assessment of primary and secondary outcomes related to neonatal and maternal health, and will collect the completed pictorial diaries and any unused misoprostol tablets from the participants before leaving. While efforts will be made to collect data on day 29, this in-person visit will be attempted up until day 43 post-natal age, if necessary. If, after two to three consecutive visits, the study team cannot reach a participant household by day 43, the day 29 questionnaire may be completed over the phone by the field supervisor that presides over the districts in which these participants live. However, if a participant cannot accommodate the time required to complete the questionnaires involved with the day 29 visit by phone or in person before or on day 43 of the newborn’s life, or if the participant is lost to follow-up following the notification of birth, a modified vital outcomes questionnaire will be administered to participants, if possible, either in-person or over the telephone, to confirm whether their baby survived the neonatal period.

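### Kit harms other than death, omphalitis and PPH are left to passive reporting, and two sections disagree on which adverse events the DSMB receives, so an arm comparison of these harms would be incomplete and unreliable

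*Protocol article*

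**What the plan says.** Under Adverse event reporting, the protocol article states: "The study will employ a passive adverse event reporting system". The trigger for a record is a report from outside: "Should any potential adverse event be reported to the study team, a data collector or field supervisor will complete an Adverse Event Report Form". The form goes to a study physician. The next step is conditional: "If deemed to be study-related, the study physician will inform the principal investigator". From there, "The principal investigator will notify the DSMB about study related adverse events".

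Under Data monitoring & interim analysis, the written report sent to the DSMB before each annual meeting is said to include "information pertaining to any adverse events that may have occurred". No relatedness condition appears there.

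Under Data collection and data management, two structured contacts follow the birth. Around day 8, "field supervisors will attempt to complete phone interviews with participant households". Later, "Data collectors will visit participant households on day 29". Neither contact is limited to one arm. Under Study outcome measures: "Study outcomes (Table 2) will be measured on all enrolled participants". Table 2 does not list burns, skin reactions or medicine side effects as outcomes.

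**The concern.** Families in the intervention arm receive self-administered misoprostol, a topical antiseptic, an oil used daily for four weeks and a warmer that heats to about 50 °C. Each could cause a non-fatal problem that is none of the outcomes compared between arms. For such problems the article describes one source only, namely what a family happens to volunteer.

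Two things can then distort the count. First, volunteering is likely to differ by arm. Intervention families have a kit to comment on and, as the Study design section says, are the only ones asked about its use. Second, relatedness to a kit that control families never receive is bound up with arm. A count filtered on relatedness is therefore not a like-for-like count.

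What is at stake is the DSMB's view of non-fatal harms during the trial and the weight that any later statement about the kit's tolerability could bear. The disagreement between the two sections adds to this, because a reader cannot tell whether the board receives the filtered or the unfiltered set.

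**Working it through.** **Step 1: what is compared by arm, and what is not.** The article states no figure that bears on this point, so the main check is a reading of its sections against each other.

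| Type of event | How it is found | Compared by arm? |
|---|---|---|
| Neonatal death, omphalitis, PPH | Outcome measurement in all enrolled participants | Yes, by risk ratios (Statistical analysis plan) |
| Hypothermia, cold stress and fever by ThermoSpot | Sticker readings | No, described in the intervention arm only |
| Burns, skin reactions, medicine side effects and similar | Volunteered reports only | No comparison described; a form can be raised in either arm |

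The gap is the last row.

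**Step 2: which events reach the DSMB.** Adverse event reporting runs in three steps: form to physician, physician to principal investigator if related, principal investigator to DSMB for related events. It describes no route for an event rated unrelated. Data monitoring & interim analysis describes a periodic report on any adverse events. The two can be made compatible only by assuming a second, unfiltered channel that neither section sets out.

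**Step 3: illustration of size.** The event risks and capture rates below are assumptions. Enrolment, number of clusters and ICC are from the article.

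- Women per arm: 27,448 / 2 = 13,724.
- Women per cluster: 27,448 / 77 = 356.5.
- Design effect with the stated ICC of 0.002: 1 + (356.5 − 1) × 0.002 = 1.71.
- Effective number per arm: 13,724 / 1.711 ≈ 8,021.

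*Chance of seeing nothing.* A harm in 1 per 1,000 kit households gives 13,724 × 0.001 = 13.7 events.

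- At 10% capture: 1.4 expected reports, and a chance of none of exp(−1.37) = 0.25.
- At 20% capture: 2.7 expected reports, and a chance of none of exp(−2.74) = 0.06.
- At 90% capture: 12.4 expected reports.

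*Power to see a doubled risk.* Two-sided 5% test of two proportions, normal approximation, 8,021 effective women per arm. The recorded risks are p1 = capture × control risk and p2 = 2 × p1. Power = Φ[(|p1 − p2| − 1.96 × SE0) / SE1], where SE0 uses the pooled risk and SE1 the separate risks.

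| True control risk | Power, 10% capture | Power, 90% capture |
|---|---|---|
| 0.1% | 0.08 | 0.34 |
| 0.25% | 0.13 | 0.69 |
| 0.5% | 0.21 | 0.94 |
| 1% | 0.37 | 0.999 |

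*Unequal reporting with no true effect.* Take a true risk of 1% in both arms and 10% capture in the control arm: 13,724 × 0.01 × 0.10 = 13.7 control reports. If kit families are 1.5 to 3 times as likely to report, the kit arm yields 20.6 to 41.2 reports. The apparent risk ratio is 1.5 to 3 although nothing differs.

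Low capture alone costs power. Unequal capture gives bias, which a larger sample does not remove.

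**The case against.** The best case for the plan has five parts.

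1. **The serious harms are covered.** A net adverse effect on death, cord infection or bleeding would show in outcomes measured in both arms. Interim analyses look at these outcomes, and a mortality gap above 40% either way unmasks the DSMB. This stands, and it limits the point to other, mostly non-fatal harms. A reader might infer that no kit harm can be compared by arm; the documents do not support that.

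2. **The relatedness filter may apply only to prompt notification.** The periodic report may be a separate, unfiltered channel. Nothing says that unrelated events are discarded. This stands in part. A reader might infer that unrelated events never leave the physician's desk, but the data monitoring section points the other way. What remains is a mismatch in wording that must be resolved.

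3. **Control families can report too.** All participants receive contact details, and the form is not restricted to one arm. This stands: to say there is no comparison group at all would go too far. Unequal reporting remains likely. Nor do the documents say that the study physician knows the allocation; that would be an inference from the open-label design. The arm-dependence of relatedness does not need it, because a report that mentions a kit item reveals the arm.

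4. **Passive reporting is a defensible choice in a pragmatic trial of this size.** The aim is effectiveness, and most of the components were used in the pilot. This is fair. However, the pilot kit as listed had no misoprostol and a different blanket, so it was not the same package.

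5. **The article is condensed, and the questionnaires are not shown.** The forms may already ask about harms. That is possible, but the article states outright that the system is passive, and a fuller document would have to depart from that sentence to close the gap.

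**Conclusion.** The concern holds in a limited form. Harms outside neonatal mortality, omphalitis and PPH have no solicited ascertainment described, and a comparison of them by arm would be incomplete and open to differential reporting, though not impossible. Separately, the two sections do not agree on whether the DSMB receives all adverse events or only those deemed study-related.

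The size cannot be taken from the documents. The capture rates of 10%, 20% and 90%, the event risks and the reporting ratios are assumptions, and the results follow from them. They show direction: weak capture hides moderate harms, and unequal capture can produce an apparent effect of any size. The primary analysis is not affected. This is an inexpensive improvement to safety data, not a flaw that invalidates the trial.

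**What to change.** 1. Add the same short closed list of harm questions to the day 8 and day 29 forms in both arms. Word them by event (for example any burn or any skin reaction) and not by kit item, so that control families can answer them on the same terms.
2. Tabulate all recorded adverse events by arm for the DSMB, with the relatedness rating as a column and not as a condition of entry. Mark which events were solicited and which were volunteered.
3. Reconcile the Adverse event reporting and Data monitoring & interim analysis sections so that both state which events the DSMB receives, and by which route (prompt notification or periodic report).

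**Cost.** A few items on existing paper forms, matching database fields and double entry, brief retraining and an amendment. No new visits or staff are needed. Enrolment has already begun, so ascertainment will differ before and after the change, and harms should be reported by period. Data collectors remain unblinded, so identical closed questions reduce differential reporting but do not remove it.
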